#### Primary Outcomes: Feasibility and Acceptability

As the main purpose of the SmartManage study is intervention development, quantitative primary outcomes are focused on participant engagement in phase 2 (pilot testing). For the adapted SmartManage CBSM for HIV and cancer intervention to be considered feasible, 70% of the participants who begin the intervention will attend at least 70% of all intervention sessions, and 85% of the enrolled participants will be retained throughout the study. These proportions are based on previously successful CBSM trials in other populations [21-23]. We will also examine cost indicators of implementation feasibility by documenting personnel time, space requirements (eg, for intervention delivery and study administration), and supply costs, including the maintenance and management of the SmartManage website.

We will evaluate intervention acceptability in two ways: (1) the proportion of eligible SMM in phase 2 who agree to participate versus decline (≥30%) and (2) via 2 exit surveys administered after participants have completed the SmartManage intervention. One such survey is the commonly used Usefulness, Satisfaction, and Ease of Use (USE) questionnaire [24], which assesses participants’ impressions of the intervention’s usefulness, ease of use, ease of learning, as well as overall satisfaction with the intervention. We also created an intervention-specific measure to evaluate participants’ views on SmartManage elements that are not assessed in the USE questionnaire. These include perceptions of relevance to health needs, how helpful the program is for SMM with HIV and cancer, and the willingness to recommend the program to similar peers. Both intervention acceptability measures ask participants to rate items on a 7-point Likert scale ranging from *strongly agree* to *strongly disagree*. Both measures also include qualitative questions with open text response fields allowing participants to share thoughts on what they found most and least helpful, what important areas were not addressed sufficiently, and recommendations to improve the intervention.

#### Secondary Outcomes: Intended Effects of Intervention, Other Psychosocial Factors, and Nature of Illness

##### Intended Effects of Intervention

This study is not intended to test the efficacy of SmartManage; however, we will examine the intended treatment effects of the intervention. We expect that relative to the educational control condition, SMM who participate in SmartManage-based CBSM for HIV and cancer will show improvements in health behaviors, HRQoL or disease-related distress, stress, and coping. Health behaviors include adherence to HIV medication regimen, as measured by the AIDS Clinical Trials Group HIV medication adherence measure [25], and frequency and duration of exercise, as measured by the International Physical Activity Questionnaire-Short Form [26]. HRQoL is captured by two measures: Functional Assessment of Cancer Therapy Scale–General [27] and Medical Outcomes Study HIV Survey [28]. Both measures assess illness-related physical, social, and functional well-being as influenced by cancer or HIV, respectively. We will also capture the impact of sexual dysfunction by using the Patient-Reported Outcomes Measurement Information System—Bother Regarding Sexual Function scale [29]. The general stress level over the past 30 days will be measured using the Perceived Stress Scale-14 [30]. Finally, aspects of distress and coping will be assessed using two measures: the Impact of Event Scale [31], which asks participants how much they have been bothered over the past week by memories and intrusive thoughts about past stressful events, and the Coping Self-Efficacy Scale [32], which measures the confidence that one can use a wide range of coping strategies when faced with adversity. Table 1 lists the study measures.

##### Other Psychosocial Factors

Although the SmartManage CBSM for HIV and cancer intervention is designed to address common targets of psychotherapy (stress management and coping skills), we will also conduct exploratory analyses to examine more stable and dispositional factors that may moderate intervention effects. Among these are the frequency and emotional impact of chronic social stigma and bias, which will be measured using the Everyday Discrimination—Sexual Orientation instrument [33], modified to include sexual orientation-specific questions. We will also look at the acculturation level using the Bidimensional Acculturation Scale [34], which assesses *Americanism* and *Hispanicism* independently to categorize individuals according to the quadrant model of acculturation by Berry [35]. This is particularly relevant in Miami-Dade County, where >53% of residents are foreign born and nearly 70% identify as Hispanic [36].

##### Nature of Illness

The target population for SmartManage for HIV and cancer is likely to be more heterogeneous than that of prior CBSM studies, given the widely varying impact of different cancer types. Therefore, we will examine the variability in intervention responses based on specific types of cancer (eg, prostate vs lung). We will also explore the practical and psychological impact of COVID-19 using 1 measure specifically for patients with cancer and 1 to assess how COVID-19 has affected the sexual health and behavior of SMM, both developed by [name] et al ([name], unpublished data, May 2020).

### Data Analytic Plan

#### Aim 1: Conduct Usability Testing and Finalize SmartManage for HIV and Cancer Intervention

For phase 1, we will summarize the participants’ demographic, psychosocial, and clinical information by using descriptive statistics. Audio-recorded participant responses will be transcribed, coded, and qualitatively analyzed using NVivo Pro (version 12.6; QSR International) software. Two independent raters will develop a codebook following a conventional content analysis approach in which codes emerge solely from the data. Throughout coding development, raters will use the constant comparative method to identify themes. Coding will follow an iterative process in which each preceding group will refine themes to accommodate new information until saturation is reached and raters reach consensus. The larger study team will review a summary of the findings to inform and refine the development of the program modules, program content, study documents (including recruitment materials), and study procedures.

#### Aim 2: Randomized Controlled Pilot Testing of Intervention (Feasibility, Acceptability, and Intended Effects)

For phase 2, descriptive statistics will be used to characterize the sample and inspect data quality. We will examine the amount, pattern, and randomness of missing data to determine appropriate statistical methods to handle missingness. Type 1 error will be set to 5% (α=.05) for calculating CIs and performing hypothesis testing. The α values will be adjusted for multiple comparisons, as needed.

We will examine feasibility via engagement and retention rates as well as cost indicators. Intervention acceptability will be evaluated using continuous data from the exit survey (USE questionnaire). These analyses will be primarily descriptive; however, we will use general linear modeling (eg, independent samples 2-tailed *t* test and ANOVA) to determine whether there are significant differences in feasibility and acceptability by sociodemographic, medical, and psychosocial variables. We will examine the distributions to determine whether alterations to the data analytic plan are needed, for example, using nonparametric methods. If >10% of the data are missing completely at random, we will use multiple imputation techniques.

To evaluate the intended effects of the intervention, we will analyze continuous scores on measures of stress, disease-related distress, and HRQoL. We will use paired samples *t* tests to examine whether these variables improve significantly within groups from pre- to postintervention measurement. We will use repeated measures ANOVA to determine whether these potential changes remain significant, accounting for the sociodemographic, medical, and psychosocial covariates described earlier. We will also use independent samples *t* tests to analyze potential differences in outcomes between the study groups (SmartManage intervention vs educational control). These will be analyzed using repeated measures ANOVA to explore whether effects remain when accounting for sociodemographic, medical, and psychosocial covariates.

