**Conclusions:**

We hypothesize that participants would find the intervention acceptable (compared with engagement and retention rates observed in similar CBSM studies). We also hypothesize that participants receiving the SmartManage intervention would have reduced symptom burden and improved health-related quality of life before and after treatment compared with those who do not.

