**Content related to health and health care**
“In general, how much did you like the information presented on the website?”“Were the topics we included relevant to your experience as an HIV+ cancer survivor?”“What specifically did you learn that you can use to improve your health and well-being?”“What problems or challenges do you have that were not addressed appropriately or to your satisfaction?”“What else would you like to see included on the site?”

All study procedures involving participants are intended to be completed remotely via secure Health Insurance Portability and Accountability Act–compliant video conferencing software. This includes the documentation of informed consent and administration of assessments, both of which will be captured using the secure REDCap (Research Electronic Data Capture; Vanderbilt University) platform.

The pilot study will enroll 50 SMM who are HIV positive with a history of a nonmetastatic solid tumor or blood cancer, who will be randomly assigned (1:1) to receive either 10 individual sessions of video-adapted health promotion (HP) content (educational control) or 10 group-based sessions of the SmartManage intervention facilitated by trained interventionists (Figure 1). Before randomization, participants will complete a self-report assessment battery (baseline or T1; Table 1), which they will complete again immediately after treatment (T2). Participants will be compensated US $20 for completing the T1 questionnaire, US $10 for each of the 10 intervention or control sessions, and US $30 for the T2 questionnaire, yielding a maximum of US $150 compensation for completing the study procedures.

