In addition, we believe that a web-based intervention is a significant strength; however, it is also a potential limitation. The intent of this format is to make group sessions accessible to those for whom in-person meetings are not feasible owing to physical limitations, lack of transportation, and location of residency. However, the requirement for a video-equipped device and stable internet is prohibitive for those who are most vulnerable, including those who are unstably housed. A potential solution that we used for other studies during the COVID-19 pandemic is to provide computer-equipped therapy rooms where participants can join the web-based group in a secure, private setting. This requires accessible facilities and reintroduces the travel burden, both of which may require additional creative solutions.

We expect that this study will inform the development of an intervention to specifically address the needs of an underserved and highly burdened population. This study will provide much-needed information regarding the utility and acceptability of a web-based group format, which will inform future iterations, bringing treatment options to those without access. We also expect that the information gathered will contribute to the literature by providing both qualitative and quantitative data describing the experiences and needs of a marginalized population living with multiple chronic illnesses. Although this is a relatively small sample, the lessons learned may be generalizable to other marginalized communities facing multiple challenges and may inform large-scale randomized controlled trials with long-term follow-up to assess the clinical utility of these programs.

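### The intended effects are read through 5% significance tests although the plan disclaims an efficacy test; at about 25 men per arm, estimates with confidence intervals would summarize them better

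*Protocol article*

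**What the plan says.** Under Intended Effects of Intervention the article states: "This study is not intended to test the efficacy of SmartManage; however, we will examine the intended treatment effects of the intervention". The same section nevertheless expects improvement relative to the educational control. The Conclusions of the abstract hypothesize that men given SmartManage "would have reduced symptom burden and improved health-related quality of life before and after treatment compared with those who do not".

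The Data Analytic Plan for Aim 2 sets the general rule: "Type 1 error will be set to 5% (α=.05) for calculating CIs and performing hypothesis testing". For stress, disease-related distress and HRQoL it then plans:

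- paired t tests, to see whether each arm improves significantly from before to after the intervention;
- repeated measures ANOVA with covariates, "to determine whether these potential changes remain significant";
- independent-samples t tests between arms, followed by repeated measures ANOVA to explore whether effects persist after covariates.

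The plan calls its analyses primarily descriptive only where it speaks of feasibility and acceptability. On size, "The pilot study will enroll 50 SMM who are HIV positive", "who will be randomly assigned (1:1) to receive either 10 individual sessions" of the control or 10 group sessions of SmartManage. No effect size, SD or power calculation accompanies the number 50.

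**The concern.** The two sections pull in different directions. One says efficacy is not being tested. The other makes crossing the 5% line the way in which changes in stress, distress and HRQoL are judged. The significance wording is explicit for the within-arm comparisons. For the between-arm comparison it enters only through the general alpha rule.

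A significance verdict can mislead in both directions in a sample of this size. A small or moderate true benefit would often be reported as no significant difference, which readers tend to take as no effect. A difference that does reach significance is selected for being large, so its estimate is on average too high. Neither outcome tells the reader what a pilot can usefully convey: the range of effects compatible with the data and how variable the scales are in this population.

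**Working it through.** The plan states no power or detectable difference, so there is no figure to reproduce. The check asks what a 5% verdict can deliver at the planned size.

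**Inputs from the article**
- 50 men, 1:1, so 25 per arm (Study Design).
- Alpha 0.05 (Aim 2 analysis plan).
- Retention target 85% (Primary Outcomes): 0.85 × 50 = 42.5, taken as 43 men, 22 v 21.

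**Assumptions**
- Two-sided test. The article says "independent samples 2-tailed" for the feasibility and acceptability t tests; the same is assumed for the intended effects.
- Independent men, one scale, no multiplicity adjustment.
- True effects of 0.3, 0.5 and 0.8 SD, as a range. None comes from the article.

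**Step 1. Smallest observed difference that is significant.** In SD units this is t(0.975, n1+n2−2) × √(1/n1 + 1/n2).
- 25 v 25: 2.011 × 0.283 = 0.57 SD.
- 22 v 21: 2.020 × 0.305 = 0.62 SD.

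These are also the approximate half-widths of the unadjusted 95% CI.

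**Step 2. Power.** Noncentral t with noncentrality d / √(1/n1 + 1/n2). For example, at 0.5 SD with 25 v 25 it is 0.5 / 0.283 = 1.77.

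| True effect | 25 v 25 | 22 v 21 |
|---|---|---|
| 0.3 SD | 18% | 16% |
| 0.5 SD | 41% | 36% |
| 0.8 SD | 79% | 73% |

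With 25 per arm, power passes 50% only above about 0.57 SD and reaches 80% at about 0.81 SD.

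**Step 3. Baseline adjustment.** If the T1 score is used as a covariate and correlates r with T2, the residual SD shrinks by √(1 − r²), so the effective effect is d / √(1 − r²). For a true 0.5 SD with 25 per arm:
- r = 0.5: 0.5 / 0.866 = 0.58, power 52%.
- r = 0.7: 0.5 / 0.714 = 0.70, power 68%.

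For a true 0.3 SD the same steps give 22% and 31%. The CI half-width falls from 0.57 SD to 0.57 × 0.866 = 0.49 SD at r = 0.5 and 0.57 × 0.714 = 0.41 SD at r = 0.7.

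**Step 4. Overstatement among significant results.** Trials with 25 per arm were simulated (400,000 per setting). The mean absolute difference among those with p < 0.05 was divided by the true difference.

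| True effect | Ratio |
|---|---|
| 0.2 SD | 3.4 |
| 0.3 SD | 2.3 |
| 0.5 SD | 1.5 |
| 0.8 SD | 1.1 |

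**Step 5. Multiplicity.** The article leaves adjustment of alpha to need. As an illustration, Bonferroni over three outcomes with 25 per arm lowers unadjusted power to 9% at 0.3 SD and 25% at 0.5 SD.

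**The case against.** The strongest defense is that this is largely handled. The intended effects are secondary. The efficacy disclaimer is explicit. The alpha sentence covers confidence intervals as well as tests, so intervals are evidently planned. The numerical success criteria concern attendance, retention and willingness to participate, and none depends on a p value. The power figures describe an unadjusted t test, while the plan also has a repeated measures ANOVA that uses T1 and T2.

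Much of this stands, and it limits the point to one of presentation on secondary outcomes. It does not remove it. Intervals are mentioned, but the plan never says that the intended effects will be read from them; the criterion it spells out is significance. The gain from the planned ANOVA depends on how it is read. A test of change between arms gives 41% to 61% power at 0.5 SD with 25 per arm for correlations of 0.5 to 0.7, less than baseline adjustment gives.

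Three stronger readings are tempting and are not supported:

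- **Significant results are about twice too large.** The article gives no effect size. The ratio runs from 3.4 to 1.1 over true effects of 0.2 to 0.8 SD and is near 2 only at about 0.35 to 0.4 SD.
- **Real effects will usually be missed.** This holds for the unadjusted test below roughly 0.57 to 0.62 SD. It fails for large effects, and at 0.5 SD if baseline is used well with 25 per arm.
- **A later trial will be sized wrongly.** The Discussion says only that lessons learned "may inform large-scale randomized controlled trials with long-term follow-up to assess the clinical utility of these programs". Nothing says a future sample size will rest on these effects, let alone on the significant ones.

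**Conclusion.** The point holds as a mismatch between the stated purpose and the stated criterion, and it is a cheap improvement. For small to moderate true effects, a 5% verdict at this sample size is mostly negative, and it is inflated when positive. At a true 0.8 SD both problems are modest. All the figures are conditional on assumed effects, a two-sided test and independent men, and the baseline-adjusted ones also on an assumed pre-post correlation. The feasibility and acceptability aims, which are primary, are untouched.

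**What to change.** In the Aim 2 analysis plan:

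1. Report each intended effect as a between-arm difference with its 95% CI, together with the SDs of the scale, adjusted for the T1 score that is already collected.
2. Remove significant improvement, and its persistence after covariates, as criteria for the intended effects.
3. Add, in line with the disclaimer under Intended Effects of Intervention, that neither a significant nor a non-significant result supports a conclusion on efficacy.

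Recasting the benefit statements in the abstract and the Discussion as quantities to be estimated would be consistent with this, but is optional.

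The cost is wording only; no new data are needed. The downside is that the results paper could not claim a significant effect of SmartManage.

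### Within-arm pre-post significance tests are listed as tests of the intended effects and not marked as descriptive, although the stated question is comparative

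*Protocol article*

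**What the plan says.** The Aim 2 section of the Data Analytic Plan opens this part with its purpose: "To evaluate the intended effects of the intervention, we will analyze continuous scores on measures of stress, disease-related distress, and HRQoL". It then names four analyses in this order:

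1. Paired samples t "tests to examine whether these variables improve significantly within groups from pre- to postintervention measurement".
2. Repeated measures ANOVA "to determine whether these potential changes remain significant, accounting for the sociodemographic, medical, and psychosocial covariates described earlier".
3. Independent samples t "tests to analyze potential differences in outcomes between the study groups (SmartManage intervention vs educational control").
4. Repeated measures ANOVA with covariates, applied to the between-group comparison.

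The section gives no ranking among the four and does not call the within-group results descriptive. Alpha is set at 5% for confidence intervals and hypothesis tests, with adjustment for multiple comparisons where needed.

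The hypothesis is worded as a contrast between arms. Under Intended Effects of Intervention: "We expect that relative to the educational control condition, SMM who participate in SmartManage-based CBSM for HIV and cancer will show improvements". The secondary aim in the Introduction and the hypothesis in the Abstract's Conclusions are comparative too. The Intended Effects section also limits the ambition: "This study is not intended to test the efficacy of SmartManage; however, we will examine the intended treatment effects of the intervention".

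**The concern.** A paired test within one arm asks whether that arm's T2 mean differs from its T1 mean. It does not ask whether the arms differ. T1 and T2 lie about 10 weeks of sessions apart, so the change in each arm contains calendar time, repeat questionnaire completion and study participation as well as any treatment effect. The protocol itself measures the impact of COVID-19 during the study, so a shared trend is plausible. Adjusting the same within-arm change for covariates, as in the second analysis, does not remove that trend. Randomisation does, but only in the contrast between arms.

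Significance in one arm and not in the other is likewise no test of a difference, because two arms with the same true change can fall on either side of the 5% line by chance. The plan lists the within-arm tests as evaluations of the intended effects, so a significant change in the SmartManage arm could be reported as support for the intervention where the arms do not differ. The Discussion leaves room for this: it anticipates measurable improvement in those who receive the experimental intervention and names no comparator there.

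**Working it through.** The article gives no effect size, SD, pre-post correlation or power figure, so there is no stated number to reproduce. The check asks how often the within-arm tests mislead when the treatment does nothing.

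**Inputs from the article**
- 50 participants allocated 1:1 (Study Design): 50 / 2 = 25 per arm.
- Retention target of 85% (Primary Outcomes): 25 × 0.85 = 21.25, taken as n = 21 per arm at T2.
- Alpha 0.05 (Aim 2).

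**Assumptions not in the article**
- Zero treatment effect.
- The same true standardised change, dz, in both arms.
- Independent arms, normal scores, two-sided tests, no multiplicity adjustment.

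**Step 1: one paired test.** The noncentrality is λ = dz × √21 = dz × 4.583, with 20 degrees of freedom and critical value 2.086. Let p be the probability that a noncentral t with these values exceeds 2.086, that is, of significant improvement in one arm.

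**Step 2: the misleading pattern.** With independent arms and equal change, the probability of significant improvement under SmartManage but not under control is p × (1 − p).

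| Shared change dz | λ | p | p × (1 − p) |
|---|---|---|---|
| 0 | 0 | 0.025 | 0.024 |
| 0.1 | 0.458 | 0.064 | 0.06 |
| 0.2 | 0.917 | 0.139 | 0.12 |
| 0.3 | 1.375 | 0.258 | 0.19 |
| 0.45 | 2.062 | 0.501 | 0.25 |
| 0.6 | 2.750 | 0.744 | 0.19 |
| 0.8 | 3.666 | 0.936 | 0.06 |

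The product cannot exceed 0.25, which it reaches at p = 0.5, and it falls away on both sides. These figures are per outcome.

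**Step 3: the SmartManage paired test alone.** A shared drift in SD units converts by dz = drift / √(2(1 − ρ)), with ρ the pre-post correlation. For example, a drift of 0.3 SD at ρ = 0.7 gives 0.3 / √0.6 = 0.387. For ρ from 0.5 to 0.7 and 21 per arm, the test is significant in 14% to 20% of trials at a drift of 0.2 SD, 26% to 39% at 0.3 SD and 59% to 80% at 0.5 SD. With no drift the rate is the nominal 5%.

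**Step 4: the between-arm contrast under the same conditions.** In 40,000 simulated trials per scenario (ρ = 0.6; drift 0, 0.3 and 0.5 SD; 25 or 21 per arm), t tests between arms on the T2 score and on the change score rejected in 4.8% to 5.1% of trials, whatever the drift. A shared shift cancels in the difference between arms.

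**The case against.** The strongest reply is that the valid comparison is already planned. The same paragraph specifies independent samples t tests and a covariate-adjusted ANOVA between the arms, and no rule says that within-arm significance decides. A reader might infer from the order of the sentences that the paired tests are the decisive analysis, or that the randomised comparison has been displaced. The article does not support that: order is not hierarchy, and a report that followed the plan would show the between-arm result beside the within-arm ones. This part of the reply stands. What remains is the role given to the paired tests, which the article itself states.

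Second, these outcomes are secondary and the article disclaims efficacy testing: "This study is not intended to test the efficacy of SmartManage". That limits the consequence. It does not explain why each arm's change is tested for significance, and a pilot with this disclaimer is better served by estimates with intervals.

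Third, regression to the mean might be offered as a main mechanism. The eligibility criteria set no minimum stress or distress score and no HRQoL threshold, so it could enter only through self-selection. It is a weak argument here, and the point does not need it.

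Fourth, quoting 25% alone would pick the mathematical maximum. The range must include the smaller values, and any alpha adjustment would change the figures.

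**Conclusion.** The concern holds at moderate severity. The plan lists within-arm significance tests, and a covariate-adjusted repeat of them, among its evaluations of intended effects. The question is framed by "We expect that relative to the educational control condition", and a within-arm test cannot answer it.

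The size is illustrative: roughly 6% to 25% of trials per outcome would show the one-arm-only pattern for a shared change of dz 0.1 to 0.8, with 21 completers per arm and no treatment effect. With no shared change the figure is 2.4%, close to the 2.5% that a two-sided 5% between-arm test allows in SmartManage's favour. The spread of dz is assumed, because the article reports no expected drift.

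A reader might go further and conclude that the trial lacks a valid test of the intended effects, or that it will claim efficacy from within-arm results. Neither follows, since the between-arm tests are planned and efficacy testing is disclaimed. The feasibility and acceptability outcomes are unaffected.

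**What to change.** In the Aim 2 section:

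- Report T1, T2 and change for each arm descriptively, without significance tests, and drop the repeated measures ANOVA that checks whether within-arm changes stay significant.
- Base every statement on intended effects on the between-arm difference at T2 adjusted for T1 (ANCOVA), with a 95% CI. This replaces the unadjusted independent samples t test.
- Say that separate within-arm results will not be used to infer a difference between arms, in keeping with the statement that efficacy is not being tested.

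The cost is wording. T1 scores are already collected before randomisation, and neither the sample size nor the data collection changes. The downside is fewer significant results to report.

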### Data Collection

#### Sociodemographic and Medical History or Status

Participants in both phases will report sociodemographic data including age, race, ethnicity, sex assigned at birth, gender identity, education, income, and household makeup. Participants in both phases will also self-report information about their cancer, HIV, and relevant health behaviors. This includes diagnosis dates, past and current treatments, and medication or treatment adherence. Cancer-specific questions include the type of cancer and whether their cancer has metastasized. HIV-specific questions relate to the frequency of contact with HIV care providers, current viral load, and CD4 count. We will also ask about any barriers they face regarding access to HIV care, such as difficulty obtaining medications or feeling stigmatized by health care providers. Participants in phase 2 will be reassessed after the intervention for information that may change (eg, HIV viral load and cancer prognosis). Table 1 lists all study measures collected.

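### The covariate-adjusted repeated measures ANOVA cannot show whether within-arm T1–T2 changes survive adjustment for baseline covariates: depending on coding, it tests change at covariate value zero or essentially repeats the paired t test

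*Protocol article*

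**What the plan says.** The Aim 2 part of the Data Analytic Plan sets out two within-arm steps for stress, disease-related distress and HRQoL. The first is "We will use paired samples *t* tests to examine whether these variables improve significantly within groups from pre- to postintervention measurement". The second is "We will use repeated measures ANOVA to determine whether these potential changes remain significant, accounting for the sociodemographic, medical, and psychosocial covariates described earlier". A separate pair of steps compares the arms: independent samples t tests, then repeated measures ANOVA to "explore whether effects remain when accounting for sociodemographic, medical, and psychosocial covariates".

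The covariates are given by class only. Under Data Collection the sociodemographic items are "sociodemographic data including age, race, ethnicity, sex assigned at birth, gender identity, education, income, and household makeup". Medical items are self-reported and include CD4 count and viral load. The psychosocial factors include discrimination and acculturation scores. Outcomes are measured at two time points, T1 before randomization and T2 immediately after treatment. The article does not state centring, coding of categorical covariates, use of covariate-by-time terms, or software. The section on intended effects calls these outcomes secondary and says the study is not meant to test efficacy.

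**The concern.** The plan gives the second step an inferential task: to judge whether a within-arm change still stands once covariates are taken into account. That task suits a comparison between different people, where covariates may differ between groups. It does not suit a comparison of each man with himself. His age, or his discrimination score at baseline, is the same on both sides of the T2 minus T1 difference, so it cannot create a spurious mean change.

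What the step does deliver depends on how the covariates are entered. Under one common way of fitting the model, the time effect answers a different question from the paired t test and is far less precise. A reader could then be told that a real improvement in stress or HRQoL was accounted for by covariates, when nothing of the kind had been shown.

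**Working it through.** **Inputs from the article.** Pilot size: "The pilot study will enroll 50 SMM who are HIV positive", allocated 1:1, so 25 per arm; the 85% retention target gives 0.85 × 25 ≈ 21. Two time points. "Type 1 error will be set to 5% (α=.05) for calculating CIs and performing hypothesis testing". Two-sided testing is stated for the feasibility and acceptability tests and assumed here. The article gives no effect size, SD or power for these outcomes, so there is no planned figure to reproduce. The standardised change, the covariate's mean/SD ratio and its correlation with change are all assumptions below.

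**Step 1. What the time effect is.** Let y = T2 − T1 and x be a covariate. With two time points, the time test in a repeated measures ANOVA that includes covariate-by-time terms is the test of the intercept a in y = a + b·x + error.
- x uncentred: a is the expected change at x = 0. For age this lies outside the eligible range (18 or older).
- x mean-centred: a is the sample mean change, the quantity the paired t test already tests.
- x additive only, no covariate-by-time term: x drops out of the difference. In a simulated data set the estimate was 2.006 (SE 0.851) with and without the covariate.

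**Step 2. Loss of precision when uncentred.** The SE of the intercept grows by about √(1 + (mean/SD)²):
- mean/SD = 1: √2 = 1.41
- mean/SD = 2.5 (e.g. score mean 20, SD 8): √7.25 = 2.69
- mean/SD = 5.5 (e.g. age mean 55, SD 10): √31.25 = 5.59

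**Step 3. Power.** Assume a change of 0.5 SD of the change score, n = 25, covariate unrelated to change. The paired t test has noncentrality 0.5 × √25 = 2.5 and power 67%. For the uncentred time effect:

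| mean/SD | noncentrality | power |
|---|---|---|
| 1 | 2.5/1.41 = 1.77 | 39% |
| 2.5 | 2.5/2.69 = 0.93 | 14% |
| 5.5 | 2.5/5.59 = 0.45 | 7% |

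Mean-centred, power is 67%, as for the paired test. With 21 men and a change of 0.6 SD the pattern is the same: about 74% for the paired test against 46%, 21% and 7% uncentred at mean/SD of 1, 2 and 5.5.

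**Step 4. Type 1 error.** Set the mean change to zero, n = 25, uncentred, covariate–change correlation 0.2 / 0.3 / 0.4.
- Adjusted test read alone: 16% / 30% / 51% rejection at mean/SD 5.5.
- Paired and adjusted tests both significant: 0.8% / 1.3% / 2.0–2.4% at mean/SD 5.5 (two runs), and about 1–2% at mean/SD 2.5.
- Correlation zero: adjusted test alone about 5%.

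**Step 5. Between-arm contrast.** In a simulated two-arm data set the group-by-time p value was 0.0008 with the covariate raw and with it centred. Shifting x moves the intercept, not the group coefficient.

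**The case against.** The strongest reply is that the change-at-zero reading needs uncentred covariates and covariate-by-time terms together, and that the article commits to neither. Centring and coding are details that a condensed article may leave to a fuller plan. This stands: the loss of power is conditional, and the silence on coding is not an error in itself. It does not rescue the step, though. The coding that avoids the wrong null leaves essentially the paired t test, so no choice yields the check that the sentence promises.

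A reader might also infer that the step raises the false positive rate above 5%. The planned sequence does not support that. A change can only stay significant if the paired test was significant to begin with, so the joint rejection rate at zero mean change cannot exceed that of the paired test. Inflation needs the adjusted test to be read alone and a covariate that is related to change.

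Nor do real changes always disappear. With 21 men, a 0.6 SD change, correlation 0.5 and mean/SD 5.5, the uncentred test still rejected in 46% of runs.

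Finally, not every covariate is fixed. The Data Collection section says that information that may change, such as viral load, is reassessed after the intervention, although Table 1 marks the Disease Information Form as baseline only. A covariate whose value changes between T1 and T2 could confound a pre–post change. The argument here covers baseline values and stable traits.

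**Conclusion.** The point holds in conditional form. For baseline covariates, the adjusted within-arm step cannot answer the question put to it. Uncentred with covariate-by-time terms, it tests change at covariate value zero, and power for a 0.5 SD change falls from 67% to about 7–39%. Centred or additive only, it adds essentially nothing to the paired t test; centring brings at most a small gain in precision when a covariate predicts change, with rejection at zero mean change of 5–7% for correlations of 0.2–0.4.

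These sizes rest on assumed effect sizes, covariate distributions and a single covariate. With three covariates unrelated to change (n = 21, 0.6 SD change), uncentred power was 10% at mean/SD 2 and 5% at 5.5.

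The consequence is moderate. The outcomes are secondary in a pilot that disclaims efficacy testing, the paired t tests stand in their own right, and the randomised comparison is untouched. The sentence is still worth changing, because it states an analysis and a purpose that do not match.

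**What to change.** Delete the sentence that re-tests within-arm change with covariates. Report the mean T1–T2 change in each arm with its 95% CI, and keep covariate adjustment for the between-arm contrast, where it can inform the answer.

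If covariates stay in any within-arm repeated measures model, state that they are mean-centred, report the adjusted change at the covariate means, and read covariate-by-time terms as describing who changes rather than whether the mean change survives adjustment.

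The cost is one sentence of the analysis plan and no new data. What is given up is a robustness statement that the step could not have supported.
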